**Background of Research**

*Prevalence and impacts of dysmenorrhea****.*** Primary dysmenorrhea is a debilitating condition that affects nearly half of all menstruating women worldwide.^1^ A cross-sectional survey performed in 2013 in Hong Kong (HK) found that out of 240 18–25-year-old female university students, the prevalence of dysmenorrhea was 80%.^2^ Primary dysmenorrhea has been linked to regular educational absenteeism,^3^ and the class attendance rate among women has been reported to decrease by 29%–50% during menstruation.^4^ Recurrent absenteeism has negative impacts on young women, decreasing the total contact time for learning, which may affect the quality of the educations they receive.^3^ Studies that have examined the impacts of primary dysmenorrhea on daily life have reported that adolescent women with primary dysmenorrhea experience the reduced ability to concentrate, educational disruptions,^2^ and lower academic performance.^5^ The effects of primary dysmenorrhea-associated pain extend beyond individual women to society, resulting in regular work absenteeism.^5^

*Pathophysiology of primary dysmenorrhea.* The pathogenesis of primary dysmenorrhea has been linked to abnormally elevated prostaglandin secretion.^1, 6^ Abnormally high prostaglandin levels cause frequent and dysrhythmic uterine contractions, resulting in ischemia and hypoxia, which are considered to be major contributors to primary dysmenorrhea-associated pain.^1, 7^ Aetiological studies have reported that prostaglandin production is regulated by progesterone with prostaglandins and progesterone displaying an inverse relationship.^1, 6, 8^

*Current understanding and knowledge gaps.* Our preliminary studies^9, 10^ have identified high-intensity aerobic training (HIAT) to be effective for decreasing pain and improving daily functioning and quality of life (QoL) among women with primary dysmenorrhea. However, no study has yet evaluated the effects of exercise, specifically HIAT, on absenteeism and academic performance among university students. The physiological mechanisms that underlie the beneficial effects of aerobic exercise-induced pain relief in primary dysmenorrhea also remain unclear. *The next critical steps in our research programme include (1) the evaluation of HIAT effects on absenteeism and academic performance among university students, (2) the identification of* *the underlying mechanisms associated with aerobic exercise-induced analgesia in primary dysmenorrhea, and (3) an economic evaluation to determine the cost-effectiveness of HIAT compared with a wait-list control group receiving usual care.*

**Preliminary studies.** Initially, we conducted a narrative review^11^ to identify the potential physiological mechanisms that might underlie the beneficial effects of physiotherapy interventions for pain relief in primary dysmenorrhea. We then performed a meta-analysis^12^ to understand the effectiveness of physiotherapy interventions on pain and QoL in women with primary dysmenorrhea. In our review,^12^ we identified preliminary, but not yet definitive evidence to support the effectiveness of aerobic exercise for primary dysmenorrhea management. Therefore, we conducted a study^10^ (*n* = 10) to evaluate the feasibility, safety, and preliminary effectiveness of an aerobic exercise intervention for primary dysmenorrhea. We found that a four-week, supervised, treadmill-based, aerobic exercise intervention had large, beneficial effects on primary dysmenorrhea-associated pain quality and intensity. Subsequently, we conducted a full randomised controlled trial (RCT, *n* = 70) to evaluate the effectiveness of a seven-month aerobic exercise intervention in women with primary dysmenorrhea.^9^ In this RCT,^9^ we found that one month of supervised treadmill-based aerobic exercise, supplemented with six months of unsupervised aerobic exercise, was effective for decreasing pain intensity and improving QoL and physical function relative to usual care.

***Pilot trial***: We conducted a pilot trial to examine the effects of HIAT on plasma biomarkers that have been implicated in the pathophysiology of primary dysmenorrhea. The pilot trial findings indicated a trend towards increased progesterone levels (***d*** = 0.36) and decreased levels of prostaglandin F2 alpha (PGF2α) metabolites (***d*** = 0.35) in the HIAT group compared with those in the control group, which suggested that aerobic exercise may affect primary dysmenorrhea pain through effects on these mediators.^8, 13^

Because our research has supported the beneficial effects of HIAT, and a recent pilot study suggested a link between HIAT and progesterone and prostaglandin levels, the proposed randomised, controlled cross-over trial will test the following three hypotheses: (1) HIAT for 12 weeks will lead to significant reductions in pain intensity and absenteeism and improve academic performance compared to baseline levels; (2) pain improvements will be mediated by increased progesterone levels, resulting in decreased PGF2α levels; (3) HIAT will display superior cost-effectiveness compared with usual care (Wait-list control [WLC]) for primary dysmenorrhea treatment.

**Scientific premises for the study hypotheses**

*Hypothesis 1****.*** Previous research has shown that primary dysmenorrhea-associated pain intensity can be reduced by 30 minutes of HIAT, performed three days a week at 70%–85% of the age-adjusted maximum heart rate (MHR).^10, 14^ The RCT performed by the PI of the current proposal showed that this amount of exercise had positive and beneficial effects on pain and QoL in women with primary dysmenorrhea.^9^ Our RCT demonstrated statistically significant improvements in primary dysmenorrhea-associated pain and the mental component of QoL, and the results surpassed the threshold for clinical significance.^9^ Therefore, we hypothesise that HIAT for 12 weeks will lead to significant reductions in pain intensity and absenteeism and improve academic performance compared to baseline values.

*Hypothesis 2.* The hormones that dominate menstrual cycles are affected by exercise. Several studies have found that exercise increases progesterone levels during the luteal phase.^15-18^ High-intensity exercise has been found to induce alterations in circulating progesterone levels in both young and premenopausal women.^19, 20^ Furthermore, exercise has been associated with a reduced prevalence of primary dysmenorrhea in several studies.^14, 21-24^ Our preliminary studies^9, 10^ also found that women who participated in HIAT reported more pain relief than no-treatment controls. Because high-intensity aerobic exercise can influence both progesterone levels and analgesic effects in dysmenorrhea, we propose that improvements in pain are mediated by increased progesterone levels and the resultant decrease in PGF2α levels. Our pilot data also support this hypothesis.

*Hypothesis 3*. An economic evaluation, from the HK societal and healthcare perspective, is necessary due to cultural diversity, economic dynamics, and country-specific healthcare policies.^25, 26^ Such an evaluation will assist in decision-making regarding cost-effective treatment options for the HK population. Given the evidence supporting the beneficial effects of HIAT from our preliminary studies and the findings of our recent pilot study, which suggested a link between HIAT and progesterone levels, we hypothesise that HIAT will be superior to WLC (receiving usual care), in terms of cost-effectiveness.

***Research design and recruitment.*** A mixed-methods study, including a cross-over RCT, and semi-structured focus groups, alongside economic evaluation, will be conducted. A Cross-over design will be adopted to minimize the effect of confounders and inter-individual variability (because each participant serves as their own control)^27^ and encourage participant enrolment in the trial.^28^ A mixed-methods approach will be considered because the combination of qualitative and quantitative methods can contribute to interdisciplinary and comprehensive research evidence.^29^ This trial will include: (1) a two-step screening phase for eligibility; (2) a baseline assessment (time-point [T1]); (3) 12 weeks of supervised treadmill training for the HIAT group; (4) post-treatment outcome assessments and economic evaluations at 12 weeks (T2); (5) a washout period for four weeks, followed by the cross-over of HIAT and WLC groups; (6) 12 weeks of supervised treadmill training for the WLC group; (7) outcome assessments at 28 weeks (T3); and (8) semi-structured focus groups at 32 weeks. Potential participants will be recruited via advertisements (study flyer) distributed at the Hong Kong Polytechnic University and the Education University of Hong Kong (please see upport letter) campuses and throughout the local community and by word-of-mouth.

***Sample size:*** G-Power analysis^30^ (3.1.9.2), set for an F-test (analysis of variance (ANOVA), was used to estimate the sample size required to reliably test the study hypotheses. We will enrol 130 participants (65 per group), allowing for a 30% attrition rate (the drop-out rate in our previous RCT^9^ with a seven-month follow-up was 20%–23%). For Hypothesis 1, the estimated sample size was 86 (43 per group). The power was set to 90%, the alpha level was 0.05, the drop-out rate was 30%, and effect-size was 0.60 (from our previous RCT^9^). For Hypothesis 2, based on estimated changes in progesterone levels from our pilot trial (***d*** = 0.36),^13^ the sample size required to detect differences in progesterone with 90% power at the 5% significance level is 100 (50 per group). Assuming a 30% drop-out rate, 130 participants (65 per group) would be required.

***Participants:*** Eligibility criteria are consistent with the guidelines for the diagnosis of primary dysmenorrhea established by the Society of Obstetrics and Gynecologists of Canada.^31^ Inclusion criteria include: (1) 18–24 years old; (2) non-pregnant; (3) having regular menstrual cycles with cycle lengths between 24 and 30 days; (4) experiencing an average menstrual pain intensity equal to or greater than 5 on a 0–10 Numerical Rating Scale (NRS); and (5) scoring low (< 600 metabolic equivalent tasks [MET]/week) on the short-form of the International Physical Activity Questionnaire (IPAQ).^32^ Exclusion criteria include: (1) the use oral contraceptive pills, hormonal therapy, or intrauterine devices; (2) the use of over-the-counter analgesics during menstruation to treat dysmenorrhea-associated pain, experience no pain relief with those analgesics and (3) participation in any formal exercise programme.

***Randomisation and blinding.*** An individual who is not involved in the study will develop a randomisation schedule (computer-generated) and prepare 130 sealed, opaque envelopes for allocation concealment. The sealed opaque envelopes will contain the group name (HIAT or WLC) and personal identification number (PIN). Following the baseline assessment, participants will select an envelope containing the details of their treatment allocation. The nature of the intervention is such that neither the participants nor the therapist can be blinded to the treatment allocation. A blinded examiner (research assistant [RA]) will assess study outcomes and collect saliva for the estimation of primary and secondary mediators. The RA will be trained to perform outcome assessments and saliva collection procedures by the PI and collaborators, respectively, during a full-day training workshop. Enzyme-linked immunosorbent assays (ELISAs) will be performed by a blinded research postgraduate student (RPg) on the saliva samples, which will be labelled using the PINs by Student Assistant #2. The student assistant will enter raw data into an Excel spreadsheet for analysis. Data analysis will be conducted in a blinded manner, using coded groups (Group A and Group B). The group code will be revealed only after the analyses have been completed.

***Procedure:*** Potential participants will undergo a two-step screening process. The first step will be conducted via telephone interview, using an eligibility checklist. Potentially eligible women will then be invited to an in-person screening session on the first day of their next menstrual period. During this session, women will complete the screening questionnaire and IPAQ to determine eligibility, assess baseline physical-activity levels, and obtain written informed consent and anthropometric measurements. Baseline assessments of primary and secondary outcomes and the costs and absenteeism data associated with each individual’s previous three menstrual cycles will be performed, and saliva samples will be collected. Participants will then be randomised into HIAT or WLC groups. Participants in the HIAT group will receive supervised treadmill training for the first 12 weeks of the trial. To minimise carryover effects, a four-week washout period will be observed for all study participants before cross-over. During the washout period, the HIAT group will discontinue exercise, and both groups will continue to manage pain as usual (i.e. with analgesics). After the four-week washout period, the cross-over period will begin during Week 16, and the participants initially randomised to the WLC group will receive the HIAT regimen from Weeks 14–28. Participants initially randomized to HIAT group will be instructed not to engage in exercise during the remainder of the study period (i.e. Weeks 14-28). Participants will be permitted to use analgesics for menstrual pain as needed throughout the study and will be instructed to record the dose and number of pills consumed in an electronic diary. As a diagnosis of primary dysmenorrhea can be confirmed by collecting detailed history;^33, 34^ a pelvic examination/ ultrasound will not be conducted.

***Saliva collection*.** Saliva will be collected as described in a previous study.^35^ All participants will receive salivary kits and specimen bag with participant details [name, PIN and group allocation]) and written instructions for saliva collection procedures. The RA will provide training to all participants for the collection of citric-acid stimulated saliva (approximately 5 mL). In our recent pilot trial, mediators levels were evaluated in plasma; however, in the current proposed study, these mediators will be measured in saliva. Some participants from our recent pilot trial, in which we collected plasma for the estimation of mediator levels,^13^ reported a preference for non-invasive diagnostic tests over invasive tests (blood collection) and expressed difficulty reporting to PolyU for blood collection when their menstrual periods started on weekends. Additionally, the circulating levels of PGF_2α_ in peripheral plasma are commonly very low because PGF_2α_ is inactivated during its initial entry through the lungs.^36^ Studies have reported that salivary measures provide a reliable and non-invasive method for assessing progesterone^37^ and prostaglandins.^35^ The home collection of saliva is convenient and cost-effective and can be done easily and safely without assistance.^38^ Therefore, for the current proposed study, mediators concentrations will be measured in the saliva, instead of blood plasma. Participants will be instructed to collect saliva immediately after the start of menstruation and two hours following the start of menstruation, to store samples in a freezer.^35^ The RA will transport the samples to the lab for further processing.

***Intervention.*** The exercise intervention will last for 24 weeks (12 weeks for the HIAT group and 12 weeks for the WLC group) at PolyU. Supervised treadmill (Zebris FDM-T) training at PolyU will begin on the first day of the second menstrual period (baseline assessments will be completed during the first menstrual period). Exercise sessions at PolyU will be instructed and supervised by a registered physiotherapist (RPg student). Using this supervisory method, the participant-to-research person ratio will be 1:1. The rationale for providing supervised sessions is to increase adherence to study interventions because, in our previous RCT^9^, adherence was higher for supervised sessions than for unsupervised home exercise sessions. MHR will be calculated using the conventional age-predicted formula (220 – age). To achieve the target HR, the speed of the treadmill will be gradually increased, based on the participants’ HR, which will be displayed on the treadmill, and the rating of perceived exertion (RPE). Because the current proposed study does not involve graded, incremental exercise, graded-exercise testing (such as VO_2max_ evaluation) will not be performed.

*HIAT.* Women will perform treadmill-based aerobic exercise for three days a week, at 70%–85% of MHR for 30 minutes and perceived exertion of 14–16, based on the Borg RPE scale. This range^39^ is considered to represent HIAT. Aerobic training will be preceded by warm-up exercises for 10 minutes and followed by cool-down exercises for 10 minutes, at a perceived exertion of 11.0 (Borg RPE). These exercise parameters are based on our previous studies^9,10^ and the American College of Sports Medicine guidelines.^40^

*WLC*. Women in the WLC group will be instructed to continue with their usual activities and manage their pain as normal (i.e., with analgesics).

**Outcome measures: Primary outcomes:** *Pain intensity.* Average pain intensity during the last 24 hours during menstruation will be assessed using the 0–10 NRS,^41^ with 0 representing ‘No pain’ and 10 representing ‘Worst imaginable pain’.

*Absenteeism from university*: Access to a prospective electronic diary will be provided for each participant to record university absenteeism. Electronic diaries are reported as highly acceptable and feasible to use.^44^ Significantly increased compliance and accuracy have been reported with e-diary recording compared with traditional paper diaries.^44^

*Academic performance*: Academic performance will be measured using the self-reported 20-item academic performance questionnaire, which was developed to measure the impacts of menstrual symptoms on academic performance.^45^

**Primary mediators:** *Salivary progesterone and PGF2α levels*. Salivary measures provide a reliable and non-invasive method for assessing unbound steroid hormones in humans.^37^ Salivary progesterone levels have been significantly correlated with plasma levels during the menstrual cycle and reflect free serum progesterone levels.^37^ Previous studies have identified elevated levels of PGF2α in saliva during menstruation^35^ and reported that saliva could be used as an important source of biomarkers, such as PGF2α.^42^

**Secondary outcomes:** *Concentration:* The 0–10 visual analogue scale will be used to measure the impact of dysmenorrhea on concentration,^43^ with 0 representing ‘No difficulty concentrating’ and 10 representing ‘Maximum difficulty concentrating’.

*Dysmenorrhea daily diary (DysDD)*: The 10-item, disease-specific DysDD (electronic version) measures the severity of menstrual bleeding, the use of analgesic for pelvic pain, and the impacts of menstrual pain on work/education, physical and social activities, and sleep.^46^ The DysDD has been reported to be an adequately reliable and valid tool for assessing dysmenorrhea.^47^ To minimise burden, participants will be asked to complete the DysDD only on days when their pain rating is non-zero or when rescue analgesics are taken.^46^

*Economic evaluation*. We will analyse the results of HIAT versus WLC over a 12-week, within-trial period (i.e., at T2).^28^ The cost-effectiveness for the entire 28-week time horizon will also be explored through T3 data observed in the HIAT arm and extrapolation of WLC data.^28^ The primary analysis will be conducted from a societal perspective (short-term direct costs, intervention costs, costs unrelated to the intervention [healthcare services and medication costs] and indirect costs, such as absence from work and impact on productivity due to primary dysmenorrhea).^48^ The secondary analysis will be conducted from a healthcare perspective (direct costs, including intervention costs and costs of other care, *excluding* absenteeism costs).^48^ Cost and absenteeism data that are collected at baseline (i.e., previous three menstrual cycles) will be used as predictors of future costs in the analysis. The EQ-5D-3L will be used to determine the QoL for the HIAT and WLC groups. The cost per participant will be calculated by multiplying unit costs identified from the HK government standardised national price list and resource quantities.^28^

An electronic diary (<https://forms.gle/gvoLHAoDqySQFr4GA>) will be used to record cost expenditures and work absenteeism. All participants will be provided with access to the cost diary, post-randomisation. Participants with limited access to the internet will be provided with printed hard copies of the cost and absenteeism diary, along with stamped and addressed return envelopes. Participants will be instructed to complete the diary during the week of menstruation each month. The research team members will be able to access the electronic diary to obtain a summary of the completed items for all study participants. The student assistant will contact participants by telephone for incomplete entries, to acquire additional details, or for failure to complete the diary.

**Qualitative study (semi-structured focus groups):** The qualitative study will provide insight into the participants’ experiences during and attitudes towards the study intervention. During focus group discussions, attempts will be made to identify the subjective experiences with participation in HIAT and participants’ perceived improvements in menstrual pain, university attendance, and academic performance. For this component of the research, a computer-generated randomisation schedule will be generated and utilised to identify 70 participants (from the 130 participants included in the RCT), to participate in the focus groups. Ethics approval and written informed consent will be obtained before enrolment. A total of seven focus groups will be conducted at 32 weeks post-randomisation. Each group will consist of a random sample of 8-10 participants and will last between 30 and 45 minutes. Focus groups will be conducted in private rooms at PolyU. If the coronavirus disease 2019 pandemic continues, face-to-face seminars will be replaced with virtual meetings (Zoom) to allow appropriate social distancing. Two researchers, a moderator (PI) and a co-moderator (RPg student), will conduct the focus groups, and a third research team member will take notes. The interviews will be recorded using a digital voice recorder, in addition to taking notes. Semi-structured discussion guides will be used.

***Treatment fidelity and missed sessions.*** To optimise adherence to exercise sessions at PolyU, a student assistant will contact any participant who has missed an exercise session and attempt to re-schedule that session. Following the baseline assessment, all participants will be provided with information regarding how to access and complete the electronic diaries.

***Retention plan.*** To maximise retention we: (1) will obtain the contact information of participants and any friends and relatives who may know their whereabouts, and obtaining permission to follow-up the listed contact persons; (2) include appointments for data collection in the study schedule; (3) schedule supervised exercise at convenient times; and (4) offer a remuneration of HK$ 200 to cover the costs incurred during study participation.

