**Statistical tests and anticipated results**

*Missing data and data preparation*. We will implement strategies, such as the digital diary, follow-up phone-call reminders, and providing routine encouragement to continue exercise, to minimise missing data. Missing values will be replaced with group means. All statistical analyses will be performed on an intention-to-treat basis, using SPSS (version 24).

***Hypothesis 1.*** The two phases that each participant completes during the course of a cross-over trial are typically referred to as the two study periods.^49^ First, a preliminary test will be carried to rule out carryover effects and to test our study for validity.^50^ This will be performed by estimating the sum of the values measured during the two treatment periods for each participant and compared across the groups by using an independent samples *t*-test.^49^ Second, the within-participant differences in outcome variables between the study periods will be calculated using a two-sided Student’s unpaired *t*-test.^49, 50^ Treatment effects will be evaluated using an ANOVA with a mixed-effects model considering the longitudinal repeated measures, including the effects of time (T1, T2, and T3) within each study group and the interaction between time and intervention. Post hoc analysis using the Bonferroni correction will be performed. Hypothesis 1 will be supported if significant reductions in pain intensity and university absenteeism and a significant improvement in academic performance are reported following 12 weeks of HIAT compared with baseline measurements.

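### No eligibility criterion requires university enrolment although recruitment reaches the general community, so two of the three primary outcomes that Hypothesis 1 needs are undefined for some eligible women.

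*Protocol*

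**What the plan says.** **Aim.** Under *Current understanding and knowledge gaps*, the first next step is to evaluate the effect of high-intensity aerobic training (HIAT) on absenteeism and academic performance in university students.

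**Recruitment.** Under *Research design and recruitment*, flyers are "distributed at the Hong Kong Polytechnic University and the Education University of Hong Kong" and then, beyond those two sites, "campuses and throughout the local community and by word-of-mouth".

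**Eligibility.** Under *Participants*: "Inclusion criteria include: (1) 18–24 years old; (2) non-pregnant; (3) having regular menstrual cycles with cycle lengths between 24 and 30 days". The fourth criterion is average menstrual pain of at least 5 on the 0–10 scale. The fifth is "scoring low (< 600 metabolic equivalent tasks [MET]/week) on the short-form" of the physical activity questionnaire. The three exclusions concern hormonal contraception or intrauterine devices, an analgesic condition, and formal exercise programmes. Student status appears in none of the eight.

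**Primary outcomes.** Under *Outcome measures* these are pain intensity, absenteeism from university (an electronic diary given to every participant) and academic performance (a self-reported 20-item questionnaire).

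**Success rule.** Under *Statistical tests and anticipated results*: "Hypothesis 1 will be supported if significant reductions in pain intensity and university absenteeism and a significant improvement in academic performance" are found after 12 weeks of HIAT relative to baseline. All three are needed.

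**Missing data.** The same section sets intention-to-treat analysis and states: "Missing values will be replaced with group means".

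**The concern.** Eligibility does not secure the population that the outcomes presuppose. A woman of 19 who works full time can see a community flyer, meet every listed criterion and be randomised. She has a pain score, but she has no university to be absent from, and the academic questionnaire has nothing to refer to.

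Hypothesis 1 is judged on all three outcomes together, so such a woman contributes to one of the three. The protocol does not say whether her other two values are missing, zero or not applicable, and each answer gives a different analysis. Under intention-to-treat, the only written rule that could apply is group-mean filling, which adds no information and makes the standard error too small. Her inclusion also moves the study population away from the one named in the aim.

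**Working it through.** There is no figure in the plan to reproduce on this point. The check is a comparison of sections, followed by an illustration of size.

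**Step 1: can a non-student be eligible?**

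| Item | Protocol section | Restricts to students? |
|---|---|---|
| Campus flyers | Research design and recruitment | In practice, largely |
| Local community, word of mouth | Research design and recruitment | No |
| Inclusion: age, not pregnant, cycle length, pain, low activity | Participants | No |
| Exclusion: hormonal or intrauterine contraception, analgesic condition, formal exercise | Participants | No |

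The answer is yes.

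**Step 2: does the protocol assume everyone is a student?** It does. The diary for university absence goes to each participant. The focus groups draw 70 women at random from all 130 and ask about university attendance and academic performance. The work absenteeism recorded under *Economic evaluation* serves the cost analysis and does not replace the primary outcome.

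**Step 3: size if undefined values are filled with group means.** The inputs are n = 65 per group (*Sample size*) and an assumed number m of students per group. The documents give no share, so a range is used: m = 58, 52 or 46, which is 11%, 20% or 29% non-students (10%, 20% and 30% rounded to whole women). Other missingness is ignored, and a normally distributed outcome compared between two groups is assumed.

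Filling n − m values with the mean leaves the sum of squares unchanged but divides it by n − 1 instead of m − 1. The standard error then uses n instead of m:

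SE ratio = √((m − 1)/(n − 1)) × √(m/n)

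- m = 58: √(57/64) × √(58/65) = 0.944 × 0.945 = 0.89
- m = 52: √(51/64) × √(52/65) = 0.893 × 0.894 = 0.80
- m = 46: √(45/64) × √(46/65) = 0.839 × 0.841 = 0.71

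By normal approximation, the actual two-sided error of a nominal 5% test is 2 × (1 − Φ(1.96 × ratio)):

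- 1.96 × 0.891 = 1.75, giving 0.081
- 1.96 × 0.798 = 1.56, giving 0.118
- 1.96 × 0.705 = 1.38, giving 0.167

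That is about 8%, 12% and 17% per outcome. A simulation of the two-group t-test with 20,000 replicates agrees with these to the nearest percentage point.

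**Step 4: size if non-students enter zero absences throughout.** Their change is zero, so the mean change in absenteeism is (1 − s) times that among students. For s = 10%, 20% or 30% the effect falls to 90%, 80% or 70% of its size.

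**The case against.** **The non-student share may be small.** Two campuses are named, the age range is 18–24, sessions are held at one of the universities, and the aim speaks of students. The telephone eligibility checklist and screening questionnaire are not shown and might ask about enrolment. This stands as a limit on size. It does not remove the gap, because a checklist applies the eligibility criteria and cannot supply one that they lack.

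**The error figures belong mainly to the imputation rule.** Group-mean filling understates the standard error for any missing value, and the protocol does not say that an inapplicable value counts as missing. This stands. The figures are conditional on that handling, and they describe a simple two-group t-test, whereas the protocol also plans a mixed-effects analysis and judges Hypothesis 1 against baseline.

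**A reader might infer that Hypothesis 1 as a whole carries an error of 8% to 17%.** The documents do not support that. The figures are per outcome, pain is unaffected, and all three outcomes must be significant, so they are at most upper bounds on a false claim caused by these two outcomes.

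**A reader might also infer that excluding non-students leaves too few women.** With 58, 52 or 46 students per group, 116, 104 or 92 are enrolled and about 81, 73 or 64 remain after 30% attrition, all below the 86 stated for Hypothesis 1. But *Sample size* lists the 30% drop-out among the inputs to that 86, so the comparison may count attrition twice. On the protocol's own convention (50 × 1.3 = 65 per group), 33 × 1.3 = 42.9 gives the stated 43 per group, which would mean about 66 evaluable women. Then 81 and 73 suffice and 64 is just short. Compared at enrolment, 116, 104 and 92 all exceed 86.

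**Non-students are informative elsewhere.** Pain, the salivary mediators and costs are defined for them, so the sponsor could keep them and restrict only the two academic analyses. That is a legitimate alternative, and a SAP could contain it. It would still leave the protocol's aim and its eligibility criteria describing different populations.

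**Conclusion.** The point holds as an inconsistency within the protocol. The aim and two of the three primary outcomes presuppose university students, while recruitment and eligibility admit women who are not. Eligibility is the protocol's own business, so an unseen SAP does not cure it.

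Its practical size is unknown, because it depends on a non-student share that the documents do not give. If the inapplicable values were mean-filled, shares of about 10% to 30% would bring the per-outcome standard error down to 0.89 to 0.71 of its correct value. If zeros were entered, the absenteeism effect would be diluted in proportion to the share. Neither a shortfall against 86 nor an inflated error for Hypothesis 1 as a whole is established.

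The change should be made because the gap is certain and closing it costs little, not because large harm has been shown.

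**What to change.** 1. Under *Participants*, add an inclusion criterion: currently enrolled as a university student.
2. Add the matching question to the telephone eligibility checklist named under *Procedure*.
3. Under *Missing data and data preparation*, state that if a non-student is nevertheless enrolled, absenteeism and academic performance are not applicable. She is left out of those two analyses, with no mean-filling and no zero entered.

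Requiring scheduled classes in both treatment periods would go further than the defect shown and is not needed to close it.

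The cost is one line of eligibility text, one screening question and one sentence on data handling. The downside is a slightly narrower community recruitment pool.
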